## Abstract

**Introduction:**

Post-traumatic symptoms are common among patients discharged from intensive care units (ICUs), adversely affecting well-being, increasing healthcare utilisation and delaying return to work. Non-pharmacological approaches (eg, music, therapeutic touch and patient diaries) have been suggested as candidate interventions and trauma-focused psychological interventions have been endorsed by international bodies. Neither category of intervention is supported by definitive evidence of long-term clinical effectiveness in patients who have been critically ill. This study assesses the feasibility and acceptability of using eye-movement desensitisation and reprocessing (EMDR) to improve the mental health of ICU survivors.

**Methods and analysis:**

EMERALD is a multicentre, two-part consent, pilot feasibility study, recruiting discharged ICU survivors from three hospitals in the UK. We are gathering demographics and measuring post-traumatic symptoms, anxiety, depression and quality of life at baseline. Two months after discharge, participants are screened for symptoms of post-traumatic stress disorder (PTSD) using the Impact of Events Scale-Revised (IES-R). Patients with IES-R scores<22 continue in an observation arm for 12 month follow-up. IES-R scores≥22 indicate above-threshold PTSD symptoms and trigger invitation to consent for part B: a randomised controlled trial (RCT) of EMDR versus usual care, with 1:1 randomisation. The study assesses feasibility (recruitment, retention and intervention fidelity) and acceptability (through semistructured interviews), using a theoretical acceptability framework. Clinical outcomes (PTSD, anxiety, depression and quality of life) are collected at baseline, 2 and 12 months, informing power calculations for a definitive RCT, with quantitative and qualitative data convergence guiding RCT refinements.

**Ethics and dissemination:**

This study has undergone external expert peer review and is funded by the National Institute for Health and Care Research (grant number: NIHR302160). Ethical approval has been granted by South Central-Hampshire A Research Ethics Committee (IRAS number: 317291). Results will be disseminated through the lay media, social media, peer-reviewed publication and conference presentation.

**Trial registration number:**

NCT05591625.

STRENGTHS AND LIMITATIONS OF THIS STUDYAdheres to Medical Research Council guidance for evaluating complex healthcare interventions.Mixed methods probe feasibility and acceptability enabling us to address cultural and contextual factors.Consistent with existing clinical pathways and best practice guidance.Not powered to detect between-group, clinically significant differences in post-traumatic symptoms.

## Introduction

### Background and rationale

Critically ill patients in intensive care units (ICUs) receive life-saving treatment, yet the burden of long-term physical, cognitive and mental health issues, collectively known as ‘postintensive care syndrome’, is significant.^1^ Global ICU admissions are on the rise^2^ and there is growing recognition of the need to address post-ICU survivorship as a defining challenge in 21st-century intensive care medicine.^3^ Despite this, healthcare providers often overlook this phase,^4^ resulting in multiple care transitions away from clinicians with an understanding of the underlying aetiology.^5^

Amidst the existential threat of critical illness, patients endure invasive treatments, potent psychoactive drugs, a busy and confusing environment and limited communication, leading to normal acute anxiety responses.^6^ However, a substantial proportion continue to suffer unpleasant psychological and somatic symptoms. Post-ICU discharge, 20%–25% experience symptoms similar to those of post-traumatic stress disorder (PTSD),^7^ with over 30% and 40% experiencing depression^8^ and anxiety,^9^ respectively. These symptoms can be persistent,^10^ co-occurring^11^ and are associated with adverse outcomes including reduced quality of life, increased healthcare utilisation and delayed return to work.^9 12 13^

Despite this, access to clinical psychology remains under-represented in UK ICU recovery services.^14^ Interventions like music therapy,^15^ therapeutic touch^16^ and patient diaries^17^ have been explored, but systematic reviews reveal that definitive evidence of long-term effect is lacking. Trauma-focused psychological therapies, such as eye movement desensitisation and reprocessing (EMDR), offer some promise, with meta-analyses showing significant reductions in PTSD, anxiety and depression for treating a diverse range of traumatised populations.^18 19^ EMDR is cost-effective^20^ and is internationally recommended by major organisations for trauma-related symptoms.^21–24^

Recent investigations of EMDR’s effectiveness in treating medical event-induced trauma, following cancer, stroke, cardiac events and multiple sclerosis have yielded promising but inconclusive findings.^25^ Case studies with ICU survivors^26 27^ and our own novel work with survivors of COVID-19-related critical illness^28^ also show promise, underscoring the need for systematic evaluation in this population. However, definitive evidence of benefit is not available.

### Objectives

The primary objective of the EMERALD study is to evaluate the feasibility and acceptability of an EMDR intervention for adult patients displaying traumatic stress symptoms following ICU discharge. These findings will guide the design of a robust, fully powered randomised controlled trial (RCT), aligning with Medical Research Council (MRC) guidance on evaluating complex medical interventions. Secondary clinical outcomes will inform the selection of a primary outcome for the larger trial and provide variance estimates for sample size calculations. Additionally, a light-touch observation arm will offer insights into the mental health trajectory of ICU survivors without traumatic stress symptoms 2 months after hospital discharge.

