## Methods: participants, interventions and outcomes

### Design

This is a multicentre, mixed-methods, randomised controlled pilot feasibility study, with a two-part consent process and is reported using the Standard Protocol Items: Recommendations for Interventional Trials (SPIRIT) reporting guidelines^29^ (online supplemental file 1: Reporting checklist for protocol of a clinical trial). Initially, all participants enter part A, which is an observational study, where they complete a series of mental health questionnaires at baseline, 2 months and 12 months posthospital discharge. If a participant shows symptoms of post-traumatic stress at the 2 month mark (scoring≥22 on the Impact Events Scale-Revised (IES-R)), they are invited to consider participating in part B, which is an interventional study of EMDR versus standard care. Those without post-traumatic stress symptoms at 2 months (≤21 on the IES-R) or those who decline participation in part B will be offered continuation of the observation arm. All participants from both part A and part B repeat the study assessments at 12 months posthospital discharge. See figure 1 for the participant timeline.

10.1136/bmjopen-2023-081969.supp1Supplementary data

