### Two-month posthospital discharge assessment

All participants will be requested to repeat the IES-R, PHQ-9, GAD-7 and EQ-5D-5L. These patient-reported outcome measures can be completed electronically via an emailed link or by using paper versions sent with a prepaid return envelope.

The study team will review the IES-R responses. Participants with a total score≥22, indicative of post-traumatic stress symptoms, will be approached to consider participation in an EMDR versus usual care RCT (part B).

Participants without symptoms (IES-R≤21) or those not interested or unable to participate in the RCT will continue in the observational study, completing the 12 month follow-up assessment.

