### Sample size

As this is a feasibility study, an a priori sample size calculation is not applicable. The findings will guide the sample size determination for a potential definitive RCT. Sample sizes of feasibility studies between 24 and 50 have been recommended to provide adequate estimate of SD for sample size calculation.^39 40^

To achieve this, a total of 160 patients will be enrolled in part A to assess feasibility adequately. Based on an expected incidence of 20%–25% post-ICU PTSD, we anticipate that around 40 patients will proceed to the part B RCT with an IES-R PTSD score≥22. The remaining 120 participants will continue in the observation arm, with a 12 month reassessment. Accounting for an estimated 25% mortality or loss to follow-up across all study arms, we anticipate approximately 30 participants completing the RCT and 90 participants completing the observation arm.

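### The observation arm's stated purpose covers only survivors below the IES-R cut-off at 2 months, but its entry rule also admits non-randomised participants at or above it, and the expected counts allow for none

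*Protocol article*

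**What the plan says.** Five places in the protocol article bear on who is in the observation arm.

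- **Objectives.** The arm has one stated purpose: "a light-touch observation arm will offer insights into the mental health trajectory of ICU survivors without traumatic stress symptoms 2 months after hospital discharge".
- **Abstract, Methods and analysis.** Entry is described by score: "Patients with IES-R scores<22 continue in an observation arm for 12 month follow-up".
- **Design.** After naming those at or below 21, the text adds that "those who decline participation in part B will be offered continuation of the observation arm".
- **Two-month posthospital discharge assessment.** The rule is repeated and widened: "those not interested or unable to participate in the RCT will continue in the observational study". Only people scoring 22 or more are invited to Part B, so these additional members are all at or above the cut-off.
- **12-month follow-up assessment.** Two groups are recognised: the observation group, meaning Part A alone, and the RCT, meaning Parts A and B. No third group is named.

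On numbers, the Sample size section says that "a total of 160 patients will be enrolled in part A to assess feasibility adequately". "Based on an expected incidence of 20%–25% post-ICU PTSD", it expects that "around 40 patients will proceed to the part B RCT with an IES-R PTSD score≥22", and then: "The remaining 120 participants will continue in the observation arm, with a 12 month reassessment". With 25% loss in every arm it arrives at about 30 RCT completers and 90 observation completers.

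The Data plan and analysis section says that the quantitative analysis is mainly descriptive. It does not say whether the observation group is summarised whole or split.

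**The concern.** The purpose, the entry rule and the expected size of the arm do not describe the same people. The purpose concerns those below the cut-off at 2 months. The entry rule adds people above it. The size is worked out as if there were no such additions.

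The two kinds of member are separated by the IES-R, which is also an outcome being followed. In one combined summary, a participant scoring 22 or more at 12 months could be a screen-negative with new symptoms or a screen-positive whose symptoms persisted. The first is what the objective sets out to learn, and the second is a different question. Screen-positives who are not randomised are also informative about how selective the RCT sample is, which bears on feasibility. A combined summary would not show this.

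The same omission affects the RCT. If some screen-positives do not join, the expected 40 randomised and 30 completing are too high.

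**Working it through.** **Inputs from the Sample size section.** Part A enrolment N = 160; prevalence of IES-R ≥22, p = 20% to 25%; loss 25%.

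**Input not in the article.** Part B uptake u among screen-positives. The consent expectation of more than 30% under Outcome measures is not stated for Part B. Uptake is therefore assumed, at 80%, 50% and 30% (20%, 50% and 70% not randomised), and everyone not randomised is assumed to stay in follow-up.

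**Step 1: reproduce the plan's figures.**
- Screen-positives: 160 × 0.25 = 40. Below cut-off: 160 − 40 = 120.
- Completers: 40 × 0.75 = 30 and 120 × 0.75 = 90.

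All four figures reproduce, but only with p = 25% and u = 100%. At p = 20% the split is 160 × 0.20 = 32 and 128, with 24 and 96 completers.

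**Step 2: share of the observation arm at or above the cut-off at 2 months.**
Screen-positives S = N × p; not randomised D = S × (1 − u); arm size = (N − S) + D; share = D / arm size.

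| Not randomised | p = 25%: D / arm | Share | p = 20%: D / arm | Share |
|---|---|---|---|---|
| 0% | 0 / 120 | 0% | 0 / 128 | 0% |
| 20% | 8 / 128 | 6.3% | 6.4 / 134.4 | 4.8% |
| 50% | 20 / 140 | 14.3% | 16 / 144 | 11.1% |
| 70% | 28 / 148 | 18.9% | 22.4 / 150.4 | 14.9% |

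In the population that the objective names, this share is 0% by definition.

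**Step 3: what does not change.** The number below the cut-off is N − S, which does not contain u. It is 120 at p = 25% (90 completing) and 128 at p = 20% (96 completing), whatever the uptake.

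**Step 4: what does change.** Randomised = S × u; completing = S × u × 0.75. For an illustrative u = 75%:
- p = 20%: 32 × 0.75 = 24 randomised; 24 × 0.75 = 18 completing.
- p = 25%: 40 × 0.75 = 30 randomised; 30 × 0.75 = 22.5 completing.

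The article cites a recommended range of 24 to 50 for feasibility samples, without saying whether it counts those randomised or those completing. At 75% uptake, the completers fall below 24 at both prevalences.

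**The case against.** The strongest reply is that the article states no faulty analysis. A reader might infer that the arm's 12-month trajectory will be pooled and is therefore contaminated. No section says so, and how a cohort is split for descriptive tables is commonly left to an analysis plan, which is not shown here. That stands: the problem arises only if the group is summarised as the 12-month section defines it.

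It can also be said that the Objectives already name the population. Saying that an arm informs about certain people does not make them its only members, and an abstract condenses. This weakens the contradiction but does not remove it, since no section links the objective to the ≤21 subgroup of a wider arm.

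Three stronger readings are not supported:
- That the non-randomised screen-positives are untreated. The article implies only that they receive no trial EMDR; it does not say that they receive no care.
- That everyone who declines enters the arm. The Design section says that continuation is offered, so some may leave, although the two-month section says that they continue.
- That a shift in the 12-month mean can be put in points. That would need a score gap between the groups, which the article does not give. A gap assumed at 2 months would probably overstate the 12-month difference, because the groups are selected on the 2-month score.

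It is also fair to say that no information is lost, because the IES-R is requested of all participants at 2 and 12 months, and that a whole-cohort summary of Part A is legitimate alongside a split. Both points are accepted.

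**Conclusion.** The mismatch is in the text and holds whatever an analysis plan may say. The objective describes survivors below the cut-off, the entry rule admits others, and the expected counts allow for none of them. Summarised whole, the observation group would not answer the stated objective. Between about 5% and 19% of it would be at or above the cut-off at 2 months, over assumed non-randomisation of 20% to 70% and the article's own prevalence range. These shares rest on assumed uptake and on full continuation; any who leave would lower them.

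The expected 120 below the cut-off is sound at 25% prevalence. The expected 40 in Part B is the figure that depends on full uptake.

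Severity is low. The primary objective is feasibility and acceptability, the observation arm serves an additional descriptive aim, and no test in the article rests on its summary.

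**What to change.** 1. State that the trajectory objective is answered by participants with a 2-month IES-R of 21 or less.
2. Report non-randomised participants with IES-R ≥22 as a separate group at each time point. A summary of the whole Part A cohort may be shown as well.
3. Compare that group's baseline and 2-month scores descriptively with those of the randomised participants, as a check on how selective the RCT sample is.
4. Align the Abstract, Objectives, Design, two-month and 12-month sections on who belongs to the arm, including whether continuation is offered or automatic.
5. Restate the Sample size section as 32 to 40 screen-positives, with the numbers randomised and completing tied to a stated uptake assumption. For example, 75% uptake and 25% loss give 24 to 30 randomised and about 18 to 22 completing.

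The cost is wording only. The 2-month IES-R that separates the groups is already requested of everyone. The downsides are that the non-randomised ≥22 group will be small, so its estimates will be imprecise, and that the expected RCT size will look less favourable.

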## Methods: participants, interventions and outcomes

### Design

This is a multicentre, mixed-methods, randomised controlled pilot feasibility study, with a two-part consent process and is reported using the Standard Protocol Items: Recommendations for Interventional Trials (SPIRIT) reporting guidelines^29^ (online supplemental file 1: Reporting checklist for protocol of a clinical trial). Initially, all participants enter part A, which is an observational study, where they complete a series of mental health questionnaires at baseline, 2 months and 12 months posthospital discharge. If a participant shows symptoms of post-traumatic stress at the 2 month mark (scoring≥22 on the Impact Events Scale-Revised (IES-R)), they are invited to consider participating in part B, which is an interventional study of EMDR versus standard care. Those without post-traumatic stress symptoms at 2 months (≤21 on the IES-R) or those who decline participation in part B will be offered continuation of the observation arm. All participants from both part A and part B repeat the study assessments at 12 months posthospital discharge. See figure 1 for the participant timeline.

10.1136/bmjopen-2023-081969.supp1Supplementary data

**Figure 1 F1:**
[figure not shown]
EMERALD participant timeline. CAPS-5, Clinician Administered PTSD Scale for DSM-5; EMDR, eye-movement desensitisation and reprocessing; IES-R, Impact of Events Scale-Revised; PTSD, post-traumatic stress disorder; QoL, quality of life; RCT, randomised controlled trial.

### Study setting

The study is sponsored by the University Hospital Southampton National Health Service (NHS) Foundation Trust (FT). Recruitment will occur after adult patients are discharged from three adult NHS ICUs in the UK: University Hospital Southampton, Royal Bournemouth Hospital and Poole General Hospital. The intervention will be provided through NHS psychological therapy services in proximity to the study participants, specifically Southern Health NHS FT and Dorset Healthcare University NHS FT.

### Part A participant recruitment

Recruitment is anticipated to occur between February 2023 and May 2024. Eligibility screening will target consecutive patients discharged from the participating ICUs. Research staff will approach eligible patients on hospital wards or within 2 months following hospital discharge, via a telephone call or email, providing a participant information sheet. Patients will be invited to complete an informed consent form (ICF), accessible electronically through Qualtrics on tablet devices provided by the trial team, via an emailed link or on paper to suit patient preference. This initial consent pertains to their participation in the observational study (part A), involving baseline data collection and psychometric assessments, with a follow-up evaluation at 2 months and 12 months following hospital discharge.

### Eligibility criteria

Eligibility will be determined by hospital research nurses acting under delegated authority of the local Principal Investigator. Patients will be eligible for part A if they meet the following criteria:

Survivor of an intensive care admission, who received level 3 care for >24 hours.Aged≥18 years.Capacity to provide informed consent.

Patients will be excluded if they meet any of the following criteria:

Pre-existing cognitive impairment such as dementia.Pre-existing diagnosis of psychosis.Not expected to survive beyond hospital discharge.Traumatic brain injury.

### Baseline data collection

Research staff will collect demographic data, medical history and ICU admission history following consent. All participants will complete the Impact of Events Scale-Revised (IES-R), Patient Health Questionnaire-9 (PHQ-9), Generalised Anxiety Disorder 7 (GAD-7) and the Euroqol 5 Dimension 5 Level (EQ-5D-5L).

### Two-month posthospital discharge assessment

All participants will be requested to repeat the IES-R, PHQ-9, GAD-7 and EQ-5D-5L. These patient-reported outcome measures can be completed electronically via an emailed link or by using paper versions sent with a prepaid return envelope.

The study team will review the IES-R responses. Participants with a total score≥22, indicative of post-traumatic stress symptoms, will be approached to consider participation in an EMDR versus usual care RCT (part B).

Participants without symptoms (IES-R≤21) or those not interested or unable to participate in the RCT will continue in the observational study, completing the 12 month follow-up assessment.

### 12-month follow-up assessment

Research staff will ask all participants, in both the observation group (part A only) and RCT (part A and part B), to repeat the IES-R, PHQ-9, GAD-7 and the EQ-5D-5L, at 12 months posthospital discharge. See table 1 for the full study schedule of events.

**Table 1 T1:** EMERALD study schedule of events

	Baseline	2 months postdischarge	3–9 months postdischarge	12 months postdischarge
Informed consent	X Part A	X* Part B		
Demographics	X			
IES-R	X	X		X
CAPS-5, CGI-S*		X*		X*
PHQ-9	X	X		X
GAD-7	X	X		X
EQ-5D-5L	X	X		X
EMDR intervention			X*	
IES-R, PHQ-9, GAD-7 (EMDR group only)				
Randomisation preference*		X*		
Process evaluation			X	X

X* for participants consenting to part B of the study only.

CAPS-5, Clinician Administered PTSD Scale for DSM-5; CGI-S, Clinical Global Impression of Illness Severity; EMDR, eye-movement desensitisation and reprocessing; EQ-5D-5L, EuroQol-5 Dimensions-5 Levels; GAD-7, Generalised Anxiety Disorder 7; IES-R, Impact of Events Scale-Revised; PHQ-9, Patient Health Questionnaire-9; PTSD, post-traumatic stress disorder; QoL, quality of life; RCT, randomised controlled trial.

### Part B participant recruitment

Participants scoring≥22 on the 2 month IES-R will receive a phone call or email from the study team, inviting them to consider consenting to part B, the EMDR versus usual care RCT. The part B PIS and ICF will be accessible electronically or via postal delivery. Those who consent to part B will first undergo a Clinician Administered PTSD Scale for Diagnostic and Statistical Manual of Mental Disorders, fifth edition (CAPS-5) assessment to evaluate PTSD symptoms and a Clinical Global Impression of Illness Severity (CGI-S) assessment with the Chief Investigator (CI). Additionally, participants will be asked to rate their preference for study arm strength using a Likert scale ranging from 0 to 10.

### Randomisation

Consenting participants will be randomly assigned to either receive usual care or usual care combined with EMDR, utilising an internet-based system, following their CAPS-5 assessment. A researcher outside of the study team will undertake randomisation to ensure the CI remains blinded to study group allocation. Random allocation will occur in a 1:1 ratio, designating them to the control group (CG) for usual care or the intervention group (EMDR) for usual care plus EMDR.

